### 2.4. Sample Size Calculation

Total study sample sizes of *n* = 15 have been recommended by our previous study [29], assuming an estimated mean UCSD Performance-based Skills Assessment-brief (UPSA-B) difference from baseline to follow-up of 10.6, with a standard deviation of 15.5. Under these conditions, the power of the primary analysis was 0.8, so approximately *n* = 13 was estimated (one-sample Student’s t-test). Therefore, it was decided to include a total of 15 samples, taking into account the dropouts of the study.

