## Abstract

Backgrounds: Social cognition is defined as the mental operations underlying social behavior. Patients with schizophrenia elicit impairments of social cognition, which is linked to poor real-world functional outcomes. In a previous study, transcranial direct current stimulation (tDCS) improved emotional recognition, a domain of social cognition, in patients with schizophrenia. However, since social cognition was only minimally improved by tDCS when administered on frontal brain areas, investigations on the effect of tDCS on other cortical sites more directly related to social cognition are needed. Therefore, we present a study protocol to determine whether multi-session tDCS on superior temporal sulcus (STS) would improve social cognition deficits of schizophrenia. Methods: This is an open-label, single-arm trial, whose objective is to investigate the efficacy and safety of multi-session tDCS over the left STS to improve social cognition in patients with schizophrenia. The primary outcome measure will be the Social Cognition Screening Questionnaire. Neurocognition, functional capacity, and psychotic symptoms will also be evaluated by the Brief Assessment of Cognition in Schizophrenia, UCSD Performance-Based Skills Assessment-Brief, and Positive and Negative Syndrome Scale, respectively. Data will be collected at baseline, and 4 weeks after the end of intervention. If social cognition is improved in patients with schizophrenia by tDCS based on this protocol, we may plan randomized controlled trial.

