## 2. Study Protocol

### 2.1. Trial Design

This study investigates the efficacy and safety of multi-session tDCS over the left STS to improve social cognition for patients with schizophrenia. This is a single-center trial at National Center of Neurology and Psychiatry, Tokyo, Japan. An open-label, single-arm study will be conducted on 15 participants with a diagnosis of schizophrenia based on the Diagnostic and Statistical Manual of Mental Disorders (DSM-5). We selected an open-label, single-arm design, because there is no precedent for tDCS over the left STS, and the major focus of this study is to verify the tolerability and safety of tDCS over the STS. Participants will receive 10 sessions of active tDCS in 5 consecutive days (twice per day) (see Figure 1). The study design is in accordance with the 2013 Standard Protocol Items: Recommendations for Interventional Trials (SPIRIT) Statement (Table S1) [28]. This study was registered within the Japan Registry of Clinical Trials (Trial ID: jRCTs032180026).

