#### 2.6.1. Cognition

The primary outcome is scores on the Social Cognition Screening Questionnaire (SCSQ) [30], which includes test of attributional style, and theory of mind (ToM). To evaluate ToM more accurately, we will also use False Belief Task [31], Hinting Task [32], and Autism-Spectrum Quotient (AQ) [33]. To evaluate emotion recognition, we will use the Facial Emotion Selection Test (FEST) [34]. To provide a standard metric for combining test scores into domains and comparing performance over time, Brief Assessment of Cognition in Schizophrenia (BACS) scores will be converted to z-scores, which shows performance relative to healthy people [35]. The premorbid IQ will be also estimated using the Japanese Adult Reading Test (JART) [36] (see Table 3).

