**Intervention**					
tDCS (twice/day)		X	X	X	
Assessments					
SCSQ	X				X
Hinting Task	X				X
FEST	X				X
False Belief Task	X				X
BACS	X				X
UPSA-B	X				X
PANSS	X				X
AQ	X				X
JART	X				
Adverse events	X	X	X	X	X
Prescribed drugs	X	X	X	X	X

tDCS, transcranial direct current stimulation; SCSQ, Social Cognition Screening Questionnaire; FEST, Facial Emotion Selection Test; BACS, Brief Assessment of Cognition in Schizophrenia; UPSA-B, Brief UCSD Performance-based Skills Assessment; PAMSS, Positive and Negative Syndrome Scale; AQ, Autism-Spectrum Quotient; JART, Japanese Adult Reading Test. The timepoint of follow-up evaluation will be allowed to be up to 7 days off.

**Table 3 jpm-11-00317-t003:** Primary/secondary outcomes.

Primary/Secondary	Domain	Outcome
Primary outcome	Social cognition (attributional style, theory of mind)	Social Cognition Screening Questionnaire (SCSQ)
Secondary outcome	Social cognition (theory of mind)	Hinting Task
Secondary outcome	Social cognition (theory of mind)	False Belief Task
Secondary outcome	Social cognition (emotion recognition)	Facial Emotion Selection Test (FEST)
Secondary outcome	Cognition	Brief Assessment of Cognition in Schizophrenia (BACS)
Secondary outcome	Cognition	Autism-Spectrum Quotient (AQ)
Secondary outcome	Premorbid intelligence quotient	Japanese Adult Reading Test (JART)
Secondary outcome	Functional capacity (daily-living skills)	UCSD Performance-Based Skills Assessment-Brief (UPSA-B)
Secondary outcome	Global symptoms of schizophrenia	Positive and Negative Syndrome Scale (PANSS)

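### The 0.8 power that section 2.4 gives to the primary analysis was calculated for UPSA-B, a secondary outcome; the power for the primary outcome, SCSQ, is undetermined

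*Protocol article*

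**What the plan says.** Section 2.4 takes its planning values from the group's earlier study, as a mean change given as "UPSA-B) difference from baseline to follow-up of 10.6, with a standard deviation of 15.5". It then states: "Under these conditions, the power of the primary analysis was 0.8". A one-sample Student's t-test is named, about 13 patients are derived, and the total is raised to 15 to allow for dropout. Neither alpha nor sidedness is given there or in section 2.8.

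The outcome hierarchy is consistent elsewhere. The abstract says "The primary outcome measure will be the Social Cognition Screening Questionnaire", section 2.6.1 says the same, and Table 3 has SCSQ as its only primary outcome. Table 3 lists UPSA-B as secondary, under functional capacity.

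Section 2.1 justifies the open-label, single-arm design on the ground that "there is no precedent for tDCS over the left STS". The same sentence adds that tolerability and safety are the study's main focus.

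**The concern.** The article's only power statement names one outcome in its inputs and another in its conclusion. A reader who takes section 2.4 at its word will believe that the SCSQ comparison has 80% power, and nothing in the article supports that.

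UPSA-B cannot be taken as a stand-in for SCSQ. By the article's own description it measures financial and communication skills, whereas SCSQ covers attributional style and theory of mind. Nowhere is one said to serve as a proxy for the other. The planning effect is also indirect in a second way. It comes from an earlier study, and by the article's account left-STS stimulation had not been tried before, so that study must have used another site.

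What is at stake is how the SCSQ result will be understood. A power figure attached to the wrong outcome gives a false idea of how informative that result can be.

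**Working it through.** **Inputs from section 2.4.** Mean UPSA-B change 10.6, SD 15.5, power 0.8, one-sample t-test, n about 13, enrolment 15. Alpha 0.05 is my assumption. Sidedness is not stated, so both cases are shown.

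**Step 1: reproduce the plan's figure.** The standardised change is d = 10.6 / 15.5 = 0.684. With the normal approximation, n = ((z_alpha + z_power) / d)².

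- One-sided: ((1.645 + 0.842) / 0.684)² = 13.2, with power 0.794 at n = 13.
- Two-sided: ((1.960 + 0.842) / 0.684)² = 16.8, so 17.

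With the exact noncentral t distribution (n − 1 degrees of freedom, noncentrality d√n), power for UPSA-B is:

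| Test | n = 13 | n = 15 | n for 80% |
|---|---|---|---|
| One-sided 5% | 0.751 | 0.809 | 15 |
| Two-sided 5% | 0.620 | 0.693 | 19 |

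Of these four conventions, only the one-sided 5% normal approximation gives about 13 (13.2, which strictly rounds up to 14). The arithmetic is therefore recoverable, and the 0.8 is a UPSA-B figure.

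**Step 2: look for the same inputs for SCSQ.** There are none. The only SCSQ number is the eligibility cut-off of 34 points in section 2.3, which gives neither an expected change nor the SD of a change. SCSQ power cannot be computed from the article.

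**Step 3: what the sample size can deliver for SCSQ.** Exact t, alpha 0.05. The standardised changes below are assumptions, apart from 0.684, which is the UPSA-B value carried over for comparison.

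| Assumed SCSQ change (SD of change) | n = 13, one-sided | n = 13, two-sided | n = 15, one-sided | n = 15, two-sided |
|---|---|---|---|---|
| 0.3 | 0.266 | 0.169 | 0.295 | 0.192 |
| 0.5 | 0.522 | 0.382 | 0.578 | 0.438 |
| 0.684 | 0.751 | 0.620 | 0.809 | 0.693 |
| 0.8 | 0.858 | 0.754 | 0.903 | 0.821 |
| 1.0 | 0.960 | 0.911 | 0.979 | 0.949 |

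Solving for 80% power, the detectable change is 0.68 SD one-sided or 0.78 SD two-sided at n = 15, and 0.73 or 0.85 SD at n = 13.

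**Step 4: precision.** The 95% confidence interval half-width, in SDs of the change, is t(0.975, n − 1) / √n. That is 2.145 / 3.873 = 0.55 at n = 15 and 2.179 / 3.606 = 0.60 at n = 13.

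**The case against.** The strongest reply is that this is a small first attempt at a new stimulation site whose declared main focus is tolerability and safety, so efficacy power matters little. That stands as far as consequence goes, and it supports keeping 15 patients. It does not remove the error. Efficacy is also a stated objective, SCSQ is the named primary outcome, and the article chose to claim power for the primary analysis.

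A second reply is that alpha and similar details belong in a full protocol or analysis plan. I accept that, and their absence is not the point here. The point is that a complete calculation is printed and attributed to the wrong outcome.

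Three stronger readings are tempting, and the article supports none of them:

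- **SCSQ is underpowered.** A reader might infer this from the lower rows of the table in Step 3. No SCSQ effect is given, and if the true change were 0.8 SD or more, 15 patients would give over 80% power with either sidedness.
- **The decision to run a randomised trial depends on the SCSQ result.** The abstract says only that such a trial may be planned if social cognition improves. Table 3 lists four instruments under social cognition, and no go/no-go rule is stated.
- **A null SCSQ result will be read as evidence of no effect.** The article does not say so. This is a possible misreading that the current wording invites, and no more.

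**Conclusion.** Section 2.4 is wrong as written, because it credits the primary analysis with a power figure computed for a secondary outcome. This follows from the text alone and does not depend on alpha or sidedness.

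The true power for SCSQ is undetermined. Across assumed standardised changes of 0.3 to 1.0 with 13 completers, it runs from 0.17 (two-sided) to 0.96 (one-sided). These bounds rest on alpha 0.05 and on effect sizes that I assumed.

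The matter is one of accurate statement. It should be corrected, but it does not call the sample size, endpoint or conduct of the trial into question, and I would not rank it among the most serious faults a plan can have.

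**What to change.** In section 2.4:

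1. Say that the calculation refers to the secondary outcome UPSA-B, and remove the sentence that assigns 0.8 power to the primary analysis.
2. State the alpha, sidedness and method that were used. This has to come first, because the UPSA-B and SCSQ figures must follow one convention. With a two-sided 5% t-test the UPSA-B inputs do not give 0.8 at 13 or 15 patients.
3. Describe 15 as a feasibility size, in line with the focus stated in section 2.1.
4. For SCSQ, choose one of two routes. Either give an expected change and SD with their source and recompute the power, or report the standardised change detectable with 80% power under the chosen test, together with the expected confidence interval half-width. The values are in Steps 3 and 4 above.

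The cost is a rewritten paragraph, and no extra patients are needed. The stated figure will look less favourable than a plain 0.8. If the sponsor takes the first route in item 4, it must also find a usable source for the SCSQ change.

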### 2.5. Intervention

Direct current will be transmitted through 35 cm^2^ saline-soaked sponge electrodes, and the intervention will be performed by a 1 × 1 transcranial direct current low-intensity stimulator (Model 1300 A; Soterix Medical Inc., New York, NY, USA). According to the International 10–20 electroencephalography system, in each session, the tDCS montage will place the anode in the left STS and the cathode in the contralateral supraorbital region, which corresponds to the T3 (mid-temporal) and FP2 (front-polar) regions (see Figure 2). We will apply 10 sessions of direct current of 2 mA for 20 min in 5 consecutive days (twice per day, with an interval of 30 min). The intensity, frequency, and duration of the stimulus are determined based on previous studies [29].

Trained psychiatrists or researchers will administer tDCS, and they will not evaluate any outcome measures. Neither tDCS-administrants nor participants will be aware of their treatment results until all participants have finished their follow-up evaluations.

### 2.6. Outcomes

Patients receive a psychological evaluation, including a screening evaluation, after being briefed on the purpose of the study and agreeing to participate in the study. Psychological assessment data will be collected at baseline and 4 weeks after the final stimulus (see Table 2). Baseline and follow-up evaluations will be performed by experienced psychologists who are not blinded. Although the interval between the baseline and follow-up evaluation is more than 5 weeks, which secures adequate washout period, the leaning effect of psychological evaluation will be a possible limitation.

#### 2.6.1. Cognition

The primary outcome is scores on the Social Cognition Screening Questionnaire (SCSQ) [30], which includes test of attributional style, and theory of mind (ToM). To evaluate ToM more accurately, we will also use False Belief Task [31], Hinting Task [32], and Autism-Spectrum Quotient (AQ) [33]. To evaluate emotion recognition, we will use the Facial Emotion Selection Test (FEST) [34]. To provide a standard metric for combining test scores into domains and comparing performance over time, Brief Assessment of Cognition in Schizophrenia (BACS) scores will be converted to z-scores, which shows performance relative to healthy people [35]. The premorbid IQ will be also estimated using the Japanese Adult Reading Test (JART) [36] (see Table 3).

#### 2.6.2. Functional Capacity (Daily-Living Skills)

The functional capacity will be assessed by the UCSD Performance-Based Skills Assessment-Brief (UPSA-B) [37], which consists of financial and communication skills.

#### 2.6.3. Global Symptoms of Schizophrenia

Global symptoms of schizophrenia will be evaluated by the Positive and Negative Syndrome Scale (PANSS) [38], which consists of positive syndrome, negative syndrome, and general psychopathology subscales.

#### 2.6.4. Adverse Events

Adverse events are defined as unwanted experiences seen during tDCS. Serious adverse events are defined as requiring inpatient treatment, moderate adverse events as requiring therapeutic intervention, and mild adverse events as requiring no therapeutic intervention. The treating physician will record the symptoms, date of onset, severity, treatment given, and association with research interventions. If symptoms are already present at baseline and do not worsen during tDCS intervention, they are not treated as adverse events.

All adverse events will be clinically evaluated and monitored throughout the study period. Previous studies report that the most common adverse events are itching, tingling, headache, burning sensation, and discomfort [39]. An experienced psychiatrist will check the presence and extent of adverse events and their association with tDCS before and after each session and assess safety at all visits during the intervention. We will follow up any unresolved adverse events after trial completion. The principal investigator will be responsible for addressing and explaining serious adverse events in the patient. The sub-investigators will be responsible for reporting any information related to such adverse events to the principal investigator. The principal investigator will have to report any serious adverse events to the Clinical Research Review Board, and to the Ministry of Health, Labor and Welfare. We will cease intervention on a per-patient if we observe severe adverse events and will also cease the whole study if we observe severe adverse events in two patients.

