These considerations prompt us to determine whether stimulation of skull surface above the STS, e.g., T3 or T4 (mid-temporal) of the International 10–20 electroencephalography system, would enhance social cognition in patients with schizophrenia. Moreover, intervention in the STS may affect hallucinations, as the STS is adjacent to the superior temporal gyrus (STG), and the network of cortical areas containing STGs is involved in hallucinations [27]. Therefore, we present a study protocol for an open-label, single-arm trial designed to evaluate the efficacy and safety of tDCS on the left STS. To our knowledge, this is the first attempt to administer tDCS targeting the STS in patients with schizophrenia.

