**Figure 2 jpm-11-00317-f002:**
[figure not shown]
Placement map for the intervention. tDCS montage will place the anode in the left superior temporal sulcus (STS) and the cathode in the contralateral supraorbital region, which corresponds to the T3 (mid-temporal) and FP2 (front-polar) regions in the International 10–20 electroencephalography system.

**Table 1 jpm-11-00317-t001:** Neural basis of social cognition [12,13,14,15,16,17,18,19].

Domains of Social Cognition	Neural Basis
Emotion recognition	Amygdala, superior temporal sulcus, medial prefrontal cortex, inferior occipital gyrus, etc.
Theory of mind (ToM)	Superior temporal sulcus, medial prefrontal cortex, middle temporal gyrus, etc.
Attributional bias	Orbitofrontal cortex, insular cortex, striatum, amygdala, superior temporal sulcus, etc.

**Table 2 jpm-11-00317-t002:** Study schedules.

	Study Period				
	Baseline	Intervention			Follow-Up
**Time point**	Within 2 weeks before the start of intervention	Day 1	Days 2–4	Day 5	4 weeks after the end of the last stimulation

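### The adverse-event definition and the baseline-symptom rule stop at the end of tDCS, although adverse events are to be monitored throughout the study and checked at the 4-week follow-up

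*Protocol article*

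**What the plan says.** All of the following is in the protocol article.

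- **Definition (2.6.4):** "Adverse events are defined as unwanted experiences seen during tDCS".
- **Baseline symptoms (2.6.4):** "If symptoms are already present at baseline and do not worsen during tDCS intervention, they are not treated as adverse events".
- **Monitoring period (2.6.4):** "All adverse events will be clinically evaluated and monitored throughout the study period". A psychiatrist is to check for adverse events "before and after each session and assess safety at all visits during the intervention".
- **Schedule (Table 2):** adverse events are marked in all five columns: baseline, day 1, days 2–4, day 5 and follow-up. Follow-up is "4 weeks after the end of the last stimulation", and a footnote adds: "The timepoint of follow-up evaluation will be allowed to be up to 7 days off".
- **Why safety carries weight here:** section 2.1 makes tolerability and safety the major focus, because this stimulation site has no precedent. The Introduction adds that "intervention in the STS may affect hallucinations".

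**The concern.** The definition covers a shorter period than the data collection it governs, and nothing elsewhere in the article extends it to events that begin once stimulation has ended. Staff who see a new event at the follow-up visit have one sentence telling them to monitor for it and another telling them it is not an adverse event.

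Several safety outputs depend on that definition. Serious, moderate and mild events are grades of adverse event in 2.6.4. Reports to the Review Board and the Ministry concern serious adverse events. Section 2.7 records how many people have adverse events requiring treatment. Section 2.6.4 halts the whole study when two patients have severe adverse events. If a late-onset event does not meet the definition, it reaches none of these.

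The baseline rule matters in this population. Every participant has schizophrenia, so many may have symptoms at entry. A symptom present at baseline that first worsens after day 5 would not count as an adverse event.

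**Working it through.** The plan states no figure on this point, so there is none to reproduce. The check compares the texts and adds simple arithmetic on the time covered.

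**Inputs.** 10 sessions of 20 minutes over 5 consecutive days (2.5); follow-up 28 days after the last stimulation, allowed to be 7 days off, so 21 to 35 days (Table 2); 15 participants (2.1).

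**Step 1: two readings of the definition.**

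| Reading of the definition | Time covered | Share of first stimulation day to follow-up |
|---|---|---|
| Only while current is on | 10 × 20 min = 200 min = 3.3 h | 3.33 / (33 × 24) = 0.4% |
| The whole 5-day course | 5 days | 5 / (5 + 28) = 15% |

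With the visit window, the second share runs from 5/40 = 12.5% to 5/26 = 19%.

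**Step 2: which conclusion survives both readings.**

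- Onset after day 5 is outside the definition under both. On the wider reading, the uncovered part is 28/33 = 85% of calendar days (21/26 = 81% to 35/40 = 87.5%).
- Onset between sessions is outside only under the first reading. The text leans to the second: checks are made before as well as after each session, and the baseline rule speaks of the intervention as a whole.

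**Step 3: follow a late event through the safety outputs.** Suppose a patient is admitted for psychotic worsening that begins two weeks after the last session.

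1. Under the definition, or under the baseline rule if the symptom was present at entry, this is not an adverse event.
2. Serious is a grade of adverse event that depends on inpatient treatment. What is not an adverse event cannot be a serious one.
3. It therefore falls outside the serious-event reports, the count of people with adverse events requiring treatment, and the two-patient stop. The stop uses the word severe, while the grades use serious; I take them to mean the same.
4. PANSS at the follow-up visit could show the worsening, but only as a score on a secondary outcome (Table 3). A score carries no onset date, treatment given or association with the intervention, which 2.6.4 requires for adverse events.

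**Step 4: scale.** With 15 participants, each patient left out of the count of people with adverse events requiring treatment shifts that proportion by 1/15 = 6.7 percentage points. The article gives no rate of late-onset events, so the number of such patients cannot be estimated.

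**The case against.** The strongest reply is that the operational text already covers the whole period. Monitoring runs throughout the study, Table 2 marks the follow-up visit, unresolved events are followed after completion, and the section 2.7 count carries no onset limit of its own. On this view one sentence is loosely worded and nothing is lost. **This stands in part.** A reader might infer that late events will be discarded, and the documents do not show that. They show two instructions that conflict. The reply does not remove the conflict. If the follow-up check serves only to track events that began during the course, the text becomes consistent, but new late events are then confirmed as not counting.

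Four stronger readings are tempting and are not supported:

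- **That events between sessions are excluded.** This needs the current-on reading, and the text leans the other way.
- **That 85% measures the undercount.** It is a share of days. The common events named in 2.6.4, such as itching, tingling and headache, may well cluster around sessions.
- **That the Introduction predicts delayed worsening of hallucinations.** It says only that they may be affected, with no direction and no timing. PANSS at follow-up would capture worsening still present at that visit, though not as an adverse event.
- **That both stopping rules are weakened.** The per-patient rule halts stimulation, and after day 5 none remains. Only the study-level rule is exposed, and section 2.7 separately has an independent committee review whether the trial is run safely.

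The dropout criterion for safety in 2.7 does not depend on the definition and is unaffected.

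**Conclusion.** The point holds as an internal contradiction. The definition and the baseline-symptom rule in 2.6.4 are narrower than the study-period monitoring in the same section and the follow-up check in Table 2. Under either reading of the definition, events or worsening that begin after the last session do not count as adverse events and so do not enter the safety outputs that use that term. The time left uncovered is about 28 of 33 days; the number of events affected is unknown.

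This rests on applying the two sentences literally and on the article's wording matching the full protocol, which is not shown. It deserves correction because safety is the stated major focus and the results may inform a later randomized trial.

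**What to change.** Reconcile the two sentences in 2.6.4 with the monitoring statement and Table 2:

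1. Define an adverse event as any unwanted experience with onset from the first stimulation up to the follow-up visit, whether or not it coincides with a session.
2. Apply the same period to worsening of symptoms present at baseline.
3. Use the onset date and association with the intervention, which 2.6.4 already records, to separate late or unrelated events in the reports.

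The sponsor should also confirm that the serious-event reports, the count in 2.7 and the study-level stop all use the reconciled definition. This point proposes no change to the stopping thresholds.

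**Cost:** two sentences and, if already approved in this form, a protocol modification. The follow-up check is already scheduled, so no new visit or assessment is needed. Some events unrelated to tDCS will be counted, and with a single arm there is no concurrent comparison to show how many; the association judgement has to carry that distinction.

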### 2.2. Participants

Inpatients or outpatients treated at National Center Hospital, National Center of Neurology and Psychiatry will be enrolled. Participants will be recruited by referrals from treating psychiatrists. Those psychiatrists will not have any conflicts of interest with the outcomes of this trial. The principal investigator must provide written informed consent before starting the trial. After providing the informed consent, participants will be screened by a treating psychiatrist to establish whether they meet the eligibility criteria. Participants will be given a gift certificate worth JPY 3000 per day as a reimbursement, and a gift certificate worth JPY 21000 in a total of 7 days including each tDCS session, and baseline/follow-up evaluation.

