## 3. Ethics Statement

The study will be performed according to the Declaration of Helsinki and will follow the Clinical Trials Act in Japan. The protocol has been presented for approval by the National Center of Neurology and Psychiatry Clinical Research Review Board (CRB3180006). The principal investigator (TS) will have the ultimate responsibility for providing informed consent to all research participants. All participants must agree to participate in the study. After initial review and approval (September 2018), the institution’s clinical research review committee will review the protocol and implementation at least annually. Two annual reviews have proceeded to date (https://jrct.niph.go.jp/re/bulletins/detail/312/22, https://jrct.niph.go.jp/re/bulletins/detail/312/1540). The principal investigator should submit a safety and progress report to the Review Board at least annually, and the researcher should submit the final report within 3 months of the completion of the study. These reports will include a summary of the total number of enrolled participants, serious/nonserious adverse events that occurred, and safety and monitoring committee reviews [41]. Changes related to the research protocol need to be submitted to the Clinical Research Review Board for review as a protocol modification. If a participant needs to be treated due to a moderate or severe adverse event directly caused by tDCS, the participant will receive the full cost of treatment from clinical trial insurance.

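### Need for inpatient treatment is the only test of a serious adverse event, so some grave events fall outside it and the grade of a patient already in hospital is ambiguous

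*Protocol article*

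**What the plan says.** Section 2.6.4 of the protocol article sets up one three-step scale. The upper two steps are given as "Serious adverse events are defined as requiring inpatient treatment, moderate adverse events as requiring therapeutic intervention", and the lowest as "mild adverse events as requiring no therapeutic intervention". No other criterion for seriousness appears. Death, threat to life, a prolonged hospital stay and lasting disability are not mentioned there or elsewhere in the article.

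Section 2.2 sets the population: "Inpatients or outpatients treated at National Center Hospital, National Center of Neurology and Psychiatry will be enrolled". Nothing says how the top step applies to someone who is already an inpatient.

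The label has consequences. Section 2.6.4 states: "The principal investigator will have to report any serious adverse events to the Clinical Research Review Board", and the same duty extends to the Ministry. Under section 3 (Ethics Statement), reports to the Review Board summarise events as serious or nonserious. Section 2.1 explains the choice of an open-label, single-arm design partly by saying that "the major focus of this study is to verify the tolerability and safety of tDCS over the STS".

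**The concern.** A definition of a serious adverse event should pick out the gravest events whoever has them and wherever they are treated. This one rests on a care setting, and the trial enrols patients who are already in that setting.

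Two problems follow. First, an event can be grave and still never call for inpatient treatment, either because the patient dies at once or because the event is resolved on the spot. The literal wording leaves such events out of the top grade. Second, for a current inpatient the wording does not settle whether the test is what the event needs, where the treatment was given, or whether a new admission followed.

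At stake is which events reach the Review Board and the Ministry as serious, and whether the serious/nonserious summary means the same thing for inpatients and outpatients. For a stimulation site that section 2.1 describes as having no precedent, that summary is a main product of the study.

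**Working it through.** No arithmetic applies, and the article gives no figure to reproduce. The check is to run concrete events through the scale in section 2.6.4, using the population in section 2.2.

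**Inputs**
- Mild: no therapeutic intervention needed (2.6.4).
- Moderate: therapeutic intervention needed (2.6.4).
- Serious: inpatient treatment needed (2.6.4).
- Population: inpatients and outpatients (2.2), with no stated limit on either.

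**Step 1: possible readings for a patient already in hospital.** The text does not choose among these:
- A: the event by its nature needs inpatient care, wherever the patient is.
- B: the treatment was given while the patient was an inpatient.
- C: the event led to a new admission.

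**Step 2: the same events under each reading**

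| Event | Outpatient | Inpatient, A | Inpatient, B | Inpatient, C |
|---|---|---|---|---|
| Headache treated with a tablet | Moderate | Moderate | Serious | Moderate |
| Event for which an outpatient would be admitted | Serious | Serious | Serious | Moderate |

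Under A the grade does not depend on setting. Under B a trivial event is raised to serious for an inpatient. Under C a major event is held at moderate. The grade can therefore differ by setting; whether it does depends on which reading the investigators adopt.

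**Step 3: grave events without inpatient treatment, in an outpatient**

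| Event | Literal grade |
|---|---|
| Sudden death | Not serious: no inpatient treatment was needed |
| Life-threatening event treated and resolved on the spot | Moderate |
| Lasting disability managed without admission | Moderate or mild |

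This step does not rest on choosing B or C. Reading A, the most favourable one, leaves the same gap.

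**Step 4: what depends on the label.** Reporting to the Review Board and the Ministry (2.6.4) and the summary in the reports to the Board (section 3) use the word *serious*, so the definition governs both directly. The stopping text uses another word: "will also cease the whole study if we observe severe adverse events in two patients". The scale has no *severe* grade. Section 3 does place that word above moderate: "If a participant needs to be treated due to a moderate or severe adverse event directly caused by tDCS". This suggests that the two terms may be meant as one, but the article does not say so.

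**The case against.** The strongest reply concerns the word *requiring*. It most naturally describes what the event needs, not where the patient happens to be. On that reading a headache treated with a tablet is moderate on the ward and at home alike, and the setting problem disappears. This stands in part: grading can differ by setting, but the text does not make it differ. What does not stand is that the ambiguity is harmless. The article enrols inpatients and leaves the reading open, and the gap for fatal or quickly resolved grave events remains even on the favourable reading.

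A second reply is that most life-threatening events would need inpatient care, and that section 3 commits the trial to the Clinical Trials Act. This is fair. The Act's reporting rules and the full protocol are not shown, so it cannot be concluded that such an event would go unreported. The article nevertheless states its own definition, and a fuller document would have to depart from that sentence to close the gap.

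A third reply is that other safeguards do not use the label. All adverse events are recorded and monitored (2.6.4). Section 2.7 counts people whose events require treatment, sets a dropout rate below 10% as the safety criterion, and gives an independent committee the power to stop the trial. These limit the damage. They do not replace the reporting duty that hangs on the word *serious*.

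Three stronger inferences are tempting and are not supported:
- A reader might infer that every enrolled inpatient is affected. On the setting problem, only an inpatient with a treated adverse event could be.
- A reader might convert one regraded patient out of 15 into a shift in a serious-event rate. The article plans no such rate as an outcome.
- A reader might infer that the definition corrupts the stopping rule. That follows only if *severe* there means *serious*, which is a separate inconsistency of terms.

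**Conclusion.** The definition is unsuitable as written. Its sole criterion leaves out, on a literal reading, deaths and life-threatening events that did not need inpatient treatment. It is also ambiguous for patients already in hospital, a group the trial expressly enrols.

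The reach of the defect is classification and reporting: what the Board and the Ministry receive as serious, and how the serious/nonserious summary is to be read. No efficacy endpoint or planned test is touched. The number of patients affected cannot be stated. The article gives no inpatient share, so inpatients could be anywhere from 0 to all 15 participants, and it gives no expected rate of treated or grave events. Grave events during this intervention may well be rare, but capturing them is the purpose of the definition.

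The conclusion assumes that the sentence in section 2.6.4 is the operative definition and that no unseen document overrides it. Because safety is the stated major focus and the remedy is small, the wording should be corrected.

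**What to change.** For classification and reporting, replace the single criterion in section 2.6.4 with one that does not depend on care setting. An event is serious if it results in death, is life-threatening, leads to a new hospital admission or prolongs an existing one, or causes lasting disability. State explicitly how this applies to a patient who is already in hospital when the event occurs. Keep need for treatment as a separate intensity grade, recorded alongside seriousness and not as part of it.

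Then reconcile the terms. The stopping text in section 2.6.4 and the insurance sentence in section 3 use *severe*, which the scale does not define. The sponsor should say how that word relates to the revised definition. No stopping rule or threshold is proposed here.

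The cost is one protocol paragraph and a change to the adverse-event form, with no added visits or staff. The downside is that slightly more events may need to be reported.
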